## Abstract

**Introduction:**

People who experience transient ischaemic attack (TIA) and minor stroke have limited follow-up despite rapid specialist review in hospital. This means they often have unmet needs and feel abandoned following discharge. Care needs after TIA/minor stroke include information provision (diagnosis and stroke risk), stroke prevention (medication and lifestyle change) and holistic care (residual problems and return to work or usual activities). This protocol describes a feasibility study and process evaluation of an intervention to support people after TIA/minor stroke. The study aims to assess the feasibility and acceptability of (1) the intervention and (2) the trial procedures for a future randomised controlled trial of this intervention.

**Methods and analysis:**

This is a multicentre, randomised (1:1) feasibility study with a mixed-methods process evaluation. Sixty participants will be recruited from TIA clinics or stroke wards at three hospital sites (England). Intervention arm participants will be offered a nurse or allied health professional-led follow-up appointment 4 weeks after TIA/minor stroke. The multifaceted intervention includes: a needs checklist, action plan, resources to support management of needs, a general practitioner letter and training to deliver the intervention. Control arm participants will receive usual care. Follow-up will be self-completed questionnaires (12 weeks and 24 weeks) and a clinic appointment (24 weeks). Follow-up questionnaires will measure anxiety, depression, fatigue, health related quality of life, self-efficacy and medication adherence. The clinic appointment will collect body mass index, blood pressure, cholesterol and medication. Assessment of feasibility and acceptability will include quantitative process variables (such as recruitment and questionnaire response rates), structured observations of study processes, and interviews with a subsample of participants and clinical staff.

**Ethics and dissemination:**

Favourable ethical opinion was gained from the Wales Research Ethics Committee (REC) 1 (23 February 2021, REC reference: 21/WA/0036). Study results will be published in peer-reviewed journals and presented at conferences. A lay summary and dissemination strategy will be codesigned with consumers. The lay summary and journal publication will be distributed on social media.

**Trial registration number:**

ISRCTN39864003.

Strengths and limitations of this studyThe multicentre study will enable exploration of implementation of the intervention in the context of different sites.The process evaluation is underpinned by the National Institutes of Health’s Behavioural Change Consortium treatment fidelity framework.Quantitative and qualitative methods will explore acceptability and how the intervention is implemented in practice.Participants must have the ability to converse in everyday English and read in English to participate, which may limit the generalisability of our findings.

## Introduction

Transient ischaemic attack (TIA) and minor stroke are important risk factors for stroke. Over 46 000 people experience a first TIA or minor stroke per year in the UK,^1^ 240 000 in the USA^2^ and 0.31 million in China.^3^

National guidelines promote long-term management that focuses on stroke prevention.^4–6^ However, research shows TIA and minor stroke patients feel unsupported in stroke prevention—both medication and lifestyle change—and often lack basic understanding of their diagnosis, stroke risk and preventative medication.^7^ Furthermore, many people experience a wide variety of residual impairments and unmet needs after TIA or minor stroke, including anxiety, mood/ emotional impact, fatigue, cognitive impairment, physical weakness, visual impairment and impaired speech.^8–17^ TIA and minor stroke have been also reported to impact on people’s ability to return to work, performance at work, social activities and family relationships.^12–19^ Follow-up care is variable and often inadequate with patients feeling abandoned after hospital discharge.^7^

Care needs after TIA and minor stroke include information provision (diagnosis and stroke risk); stroke prevention (medication and lifestyle change) and holistic care (residual problems and return to work or usual activities).^7^ However, there is no evidence for how to best support these patients after rapid specialist review in hospital. To address this, we developed a multifaceted intervention which aims to actively identify and address unmet needs after TIA and minor stroke: Structured follow-Up Pathway to imProve management Of Residual impairmenTs and patients’ quality of life after TIA and minor stroke. The components of the intervention are described in this protocol. In accordance with the Medical Research Council guidance on developing and evaluating complex interventions,^20^ we will evaluate the feasibility and acceptability of (1) the intervention and (2) the trial procedures for a future randomised controlled trial (RCT) of this intervention. In addition, we will conduct a process evaluation to evaluate intervention fidelity and contextual influences on delivery.

## Methods and analysis

### Study design

The study is a multicentre, individual randomised feasibility study with a mixed-methods process evaluation. The study is reported in accordance with the Standard Protocol Items: Recommendations for Interventional Trials checklist^21^ and the design is summarised in figure 1.

**Figure 1 F1:**
[figure not shown]
Trial schema.

The study opened for recruitment on September 2021 with planned completion by December 2022.

### Patient and public involvement

A core group of three people who have experienced TIA or minor stroke have supported this study from inception, with ad hoc contributions from other members of the public with TIA or minor stroke. The group supported the initial development of the research question and funding application, which were informed by their priorities and experiences. The group was involved in: selection of outcome measures; development of study documents; and design of the trial, such as recruitment strategies and considering participant burden related to data collection and attending intervention appointments. The group was integral to the intervention development, in particular the website of support services and resources. The group will continue to support the delivery of the study and dissemination of findings. One member (PC) is a coauthor and member of the study oversight committee. Patient and public involvement activities and impact will be reported using GRIPP2.^22^

### Study objectives

#### Trial design and methods

Assess feasibility and acceptability of the trial design and methods, including: number of patients meeting eligibility criteria; consent and randomisation processes; recruitment and retention rates; piloting the health economics questionnaire; and data completeness.Provide data to inform the sample size for a definitive RCT.Provide data to help inform selection of the primary outcome measure for a definitive RCT, including data completeness and correlation of the outcome measures with each other.

#### Intervention (process evaluation)

Investigate acceptability of the intervention for participants and intervention providers.Test hypotheses relating to the theoretical underpinning of the intervention.Assess if intervention providers are adequately trained to deliver the intervention.Assess adherence to the intervention.Assess contamination with the control group.Define the ‘dose’ of the intervention (ie, attendance, length of appointment and number of appointments).Explore how well intervention participants received and understood the intervention.Explore to what extent the intervention was enacted as intended by patient participants (intervention group).

### Study setting and eligibility criteria

Participants will be recruited from TIA clinics and stroke wards at three tertiary hospital sites in England, one in South East England (Berkshire) and two in North West England (Wigan and Liverpool). Participants will be adults who have experienced a first or recurrent TIA or minor stroke. The full eligibility criteria are detailed in box 1.

Box 1Eligibility criteriaInclusion criteriaAdults (aged ≥18 years).Resident in England.Diagnosis of confirmed transient ischaemic attack (TIA) or minor stroke by a stroke consultant. TIA will be defined as a transient episode of neurological dysfunction caused by focal brain, spinal cord or retinal ischaemia, without acute infarction.^30^ Minor stroke will be defined as a modified Rankin scale score ≤1 or no change in modified Rankin scale score from pre-event (to account for people who were disabled prior to their TIA or minor stroke)*.Attending the TIA clinic or stroke ward for a new diagnosis of TIA or minor stroke, rather than for a follow-up appointment.Ability to converse in everyday English and read in English.Capacity to provide fully informed consent for participation in the trial.Exclusion criteriaHistory of full stroke (modified Rankin scale score >1).History of dementia.People who lack capacity to participate, such as if they have severe memory problems that mean they would not remember giving consent or if they have severe communication problems, not precluding patients who use electronic devices to communicate.Patients receiving early supported discharge or cardiac rehabilitation.Patients receiving any palliative care.

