### Intervention

Intervention development was underpinned by the Behaviour Change Wheel theoretical framework^23^ and iteratively refined in collaboration with patient partners and a multidisciplinary team (online supplemental appendix 1, eTable 1).

10.1136/bmjopen-2021-060280.supp1Supplementary data

The multifaceted intervention broadly comprises six components (figure 2):

Training for nurses and allied health professionals (AHPs) delivering the intervention.Structured nurse or AHP led follow-up appointment, 4 weeks after TIA or minor stroke.Needs checklist completed by participants prior to the appointment.Resources to support management of needs, including a website of resources and support services; list of local support services; and a self-management booklet.Action plan.Structured letter to general practitioners (GPs) to improve the interface communication between secondary and primary care.

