#### When and how often

The intervention appointment will take place at 4 weeks (or up to 6 weeks). The appointment is expected to last approximately 30 min. One appointment will be offered initially; however, participants will have an option to attend additional follow-up if judged clinically necessary by the nurse or AHP. There are no predetermined criteria for further follow-up and the criteria used by nurses/AHPs will be recorded as part of the feasibility study to inform future refinement of the intervention.

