### Recruitment

A member of the clinical team will screen patients’ medical records and approach potentially eligible patients face to face or by phone. After confirming eligibility, potential participants will be invited to take part in the study. Informed consent may be taken face to face (for people approached in clinic), by post (for people who need more time to consider participation) or verbally (for people approached via phone). Verbal consent will be clearly documented in the participant’s medical records and the participant will also be sent a postal consent form to compete. Sites will receive a per-participant reimbursement for recruitment.

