### Randomisation

Participants will be randomised 1:1 to either the intervention or control group. A minimisation algorithm will be used within an online randomisation system to ensure balance in the treatment allocation using the following variables: age at consent (<60 years, ≥60 years); sex (male, female); diagnosis (TIA, minor stroke); employment (employed, non-employed/retired).

A ‘random element’ will be included in the minimisation algorithm, so that each patient has a probability, of being randomised to the opposite treatment that they would have otherwise received.

Participants will be randomised at baseline by clinical staff; however, to prevent baseline patient reported outcomes being affected by study arm allocation, participants will be notified of their randomisation allocation after they have returned the 1-week questionnaire or at 3 weeks (if the 1-week questionnaire is not returned). Participants will be notified of their allocation by a letter in the post, which will be sent by the research team at the Trials Unit. Due to the nature of the intervention, it is not possible to blind participants or clinicians delivering the intervention.

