**Trial design**		
Recruitment	% target sample size recruited	≥90%: proceed to a full-scale trial
		70%–89%: SOC will consider the feasibility of proceeding to a full-scale trial bearing in mind the data presented, representativeness of the sample and possible steps to increase recruitment.
		<70%: full-scale trial unlikely to be feasible
Randomisation*	% of consented participants randomised	≥90%: proceed to a full-scale trial
		70%–89%: SOC will consider the feasibility of proceeding to a full-scale trial bearing in mind the data presented, representativeness of the sample and possible steps to address randomisation issues.
		<70%: full-scale trial unlikely to be feasible
Return rate of 24 weeks questionnaire*	% of 24 weeks questionnaires returned	≥80%: proceed to a full-scale trial
		50%–79%: SOC will consider the feasibility of proceeding to a full-scale trial bearing in mind the data presented, representativeness of the sample and possible steps to increase return rates.
		<50%: full-scale trial unlikely to be feasible
Intervention		
Attendance rate*	% of intervention arm participants attending first appointment	≥90%: proceed to a full-scale trial
		70%–89%: SOC will consider the feasibility of proceeding to a full-scale trial bearing in mind the data presented, representativeness of the sample and possible steps to increase attendance
		<70%: full-scale trial unlikely to be feasible
Delivery of the intervention	% completion of: checklists, action plans, GP letters; use of directory of support services; Issues regarding delivery of the intervention components and contamination explored in qualitative interviews	The SOC will consider the quantitative and qualitative data and make an overall judgement on whether the intervention content is delivered as intended
Acceptability	% of participants reporting acceptability of intervention components on intervention feedback questionnaire; issues regarding acceptability of the intervention components explored in qualitative interviews	The SOC will consider the quantitative and qualitative data and make an overall judgement on whether the intervention is acceptable

*Critical progression criteria: the trial is unlikely to be feasible if these criteria are not met, even if other criteria are satisfactory.

GP, general practitioner; SOC, Study Oversite Committee.

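### The critical attendance criterion has no time window and Box 1 sets no limit from event to enrolment, so attendance cannot show whether follow-up at 4–6 weeks is feasible

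*Protocol article*

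**What the plan says.** All references are to the protocol article.

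- **Eligibility.** Under Study setting and eligibility criteria, the text says "The full eligibility criteria are detailed in box 1", so the list is presented as complete. Its one criterion on recency is "Attending the TIA clinic or stroke ward for a new diagnosis of TIA or minor stroke, rather than for a follow-up appointment". This restricts the type of visit, not the time since the event.
- **Recruitment.** Patients may be approached in person or by phone. Consent may be taken "by post (for people who need more time to consider participation"), and no deadline is given.
- **Timing of the intervention.** The Intervention section lists a "Structured nurse or AHP led follow-up appointment, 4 weeks after TIA or minor stroke". When and how often adds "The intervention appointment will take place at 4 weeks (or up to 6 weeks").
- **Allocation.** Under Randomisation, "Participants will be randomised at baseline by clinical staff", but "participants will be notified of their randomisation allocation after they have returned the 1-week questionnaire or at 3 weeks (if the 1-week questionnaire is not" (the clause cut off here covers non-return). The notice is a posted letter. The starting point of the 3 weeks is not stated.
- **Questionnaire clock.** Outcomes and data collection contrasts completion at 1 week with completion at baseline, which suggests that these weeks run from baseline.
- **Progression.** In Table 4 attendance is the percentage "of intervention arm participants attending first appointment". It is starred as critical, with bands at 90% and 70%, and carries no timing condition.

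**The concern.** The appointment is timed from the event, while disclosure of allocation appears to be timed from enrolment. Nothing in the eligibility list ties the two clocks together. Someone enrolled late enough is told of their allocation after the appointment window has closed, yet meets every criterion in Box 1.

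This matters because of how Table 4 measures success. The intervention is defined partly by when it happens, and attendance is one of the starred criteria on which the decision to proceed depends. A first appointment at week 5 and one at week 10 count the same. A high attendance figure would then show that people come when invited, but not that the service can see them at the time the intervention specifies. The dose outcome in Table 3 does not fill the gap: it lists attendance, length and number of appointments, but not when they took place.

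**Working it through.** The plan gives no figure to reproduce, so the check is timeline arithmetic on its own time points.

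**Inputs**
- End of window: 6 weeks after the event (Intervention; When and how often). The second section does not repeat the origin; I take it to be the event, as in the first.
- Fallback notice: 3 weeks (Randomisation), read as weeks from baseline.
- Earliest notice for someone who returns the questionnaire promptly: about 1 week from baseline.
- d = weeks from event to randomisation. Box 1 does not bound it.

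**Formulas**
- Non-returner: notice at d + 3; time left to week 6 = 6 − (d + 3) = 3 − d.
- Prompt returner: notice at about d + 1; time left = 6 − (d + 1) = 5 − d.

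| d (weeks) | Non-returner: notice at week | Weeks left | Prompt returner: notice at week | Weeks left |
|---|---|---|---|---|
| 0 | 3 | 3 | 1 | 5 |
| 1 | 4 | 2 | 2 | 4 |
| 2 | 5 | 1 | 3 | 3 |
| 3 | 6 | 0 | 4 | 2 |
| 4 | 7 | −1 | 5 | 1 |
| 5 | 8 | −2 | 6 | 0 |

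The window is therefore lost at d of about 3 or more for non-returners, and about 5 or more for prompt returners. The nominal 4-week point is tighter: for a non-returner, 4 − (d + 3) = 1 − d, so it has passed before notice once d exceeds 1.

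**Sensitivity to postal and booking time.** The article gives no figure. If I assume a lag of 0 to 1 week, the largest workable d falls from 3 to 2 weeks for non-returners (6 − 3 − 1) and from 5 to 4 weeks for returners (6 − 1 − 1).

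**Other reading of the clock.** If the 3 weeks ran from the event, someone enrolled after week 3 could be told at once, and only a person enrolled after week 6 would necessarily miss the window. The problem shrinks, but Box 1 still admits such a person.

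**What Table 4 records.** Under either reading, a participant seen after week 6 is a first-appointment attender and enters the numerator. The criterion cannot separate in-window from out-of-window delivery.

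**The case against.** The strongest reply is that few such people may exist. Recruitment is at a visit for a new diagnosis, follow-up visits are excluded, and the setting is described as rapid specialist review. Most participants would then have a small d, and even a non-returner at d = 2 has a week left. This stands: the article gives no distribution of delay, so the number affected is unknown and may be small.

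Second, nothing prevents sites from managing the timing. Staff randomise at baseline and could hold a slot before the letter goes out. Appointments may be by phone or video. The needs checklist must be completed before the visit, but the article does not require it to be sent back first. This also stands. It means the arithmetic shows when notice comes too late, not that a visit is always impossible.

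Third, an article condenses the full protocol, and the trial schema is not shown, so time origins may be stated elsewhere. That weakens any complaint about the unstated origin. It does not answer the point about Table 4, which sets out the predefined criterion without a window. Table 3 does provide for recording deviations from the intervention manual. However, that relies on a small number of observed appointments and on an intervention log for which Case report forms lists attendance, duration and number of appointments, but no date.

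Two stronger inferences are tempting. A reader might infer that late enrolment would pull attendance below the 90% band. The documents do not support this: it would require participants never to be seen at all, whereas Table 4 counts a late visit as attendance. A reader might also infer that variable delay inflates the 6-month SDs carried to the full trial. Nothing in the article allows that to be assessed, and a full trial with the same eligibility would have the same mix.

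**Conclusion.** The point holds in a limited form. Box 1, presented as complete, allows any delay from event to enrolment. The appointment is timed from the event, and notice of allocation appears to be timed from baseline. On that reading the 6-week limit is missed by non-returners randomised about 3 weeks or more after the event and by prompt returners at about 5 weeks or more, each about a week sooner if a 1-week lag is assumed. How many people this involves cannot be derived from the article.

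The firmer part does not depend on that number. A critical go/no-go measure for an intervention defined at 4–6 weeks has no time condition, so it cannot show whether delivery at that time is feasible.

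It would go too far to say that late enrollees in general cannot be seen in time, or that the eligibility criteria must be changed. The arithmetic confines the problem to particular combinations of delay and questionnaire return.

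**What to change.** 1. In Table 4, report attendance in two ways: overall, as now, and within 6 weeks of the event. The event date is already in Table 1. Use an appointment date from the intervention log, and add that field if it is absent, since Case report forms does not list it.
2. Report the distribution of the event-to-randomisation interval, so that the number of participants affected becomes known.
3. Reconcile Box 1, Intervention, When and how often, Randomisation, and Outcomes and data collection on one stated time origin for the week counts. Whether to add an enrolment limit, and at what value, is for the investigators. Recruitment had opened in September 2021, so a new criterion would change the population mid-study.

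Items 1 and 2 exclude no one. The cost is one date field if it is not already recorded, and a within-window attendance figure that may look less favourable than the overall one.

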### Intervention

Intervention development was underpinned by the Behaviour Change Wheel theoretical framework^23^ and iteratively refined in collaboration with patient partners and a multidisciplinary team (online supplemental appendix 1, eTable 1).

10.1136/bmjopen-2021-060280.supp1Supplementary data

The multifaceted intervention broadly comprises six components (figure 2):

Training for nurses and allied health professionals (AHPs) delivering the intervention.Structured nurse or AHP led follow-up appointment, 4 weeks after TIA or minor stroke.Needs checklist completed by participants prior to the appointment.Resources to support management of needs, including a website of resources and support services; list of local support services; and a self-management booklet.Action plan.Structured letter to general practitioners (GPs) to improve the interface communication between secondary and primary care.

